**Statement of Compliance**

This document is a protocol for a research project. This study will be conducted in compliance with all stipulation of this protocol, the conditions of the ethics committee approval, the NHMRC National Statement on ethical Conduct in Human Research (2007) and the Note for Guidance on Good Clinical Practice (CPMP/ICH-135/95).

## STUDY SYNOPSIS

|                             |                                                                                                                                                                                                                                                                                                                                                                                                                |
|-----------------------------|----------------------------------------------------------------------------------------------------------------------------------------------------------------------------------------------------------------------------------------------------------------------------------------------------------------------------------------------------------------------------------------------------------------|
| Title:                      | A randomised double-blind trial comparing the effectiveness of anti-androgen medications in transgender women                                                                                                                                                                                                                                                                                                  |
| Design:                     | Double-blind randomised trial                                                                                                                                                                                                                                                                                                                                                                                  |
| Study Centres:              | Austin Health                                                                                                                                                                                                                                                                                                                                                                                                  |
| Hospital:                   | Austin Health                                                                                                                                                                                                                                                                                                                                                                                                  |
| Study Question:             | Is cyproterone acetate more effective than spironolactone in lowering endogenous testosterone levels and increasing breast volume and feminine fat distribution in male-to-female individuals commencing estradiol therapy?                                                                                                                                                                                    |
| Study Objectives:           | 1. To compare the effectiveness of cyproterone acetate and spironolactone as an anti-androgen agent in male-to-female transgender individuals commencing estradiol.                                                                                                                                                                                                                                            |
| Primary Endpoint:           | Breast volume                                                                                                                                                                                                                                                                                                                                                                                                  |
| Secondary Endpoint:         | 
 
1. Percentage of individuals who have total testosterone levels <2 nmol/L (in the female reference range) at 3 and 6 months.
 
2. Fat mass including leg and gynoid regional fat;
 
3. Depression assessment using Patient Health Questionnaire 9;
 
4. Gender Dysphoria using the Gender Preoccupation and Stability Questionnaire.
 
 |
| Inclusion Criteria:         | 
 
1. Male-female individuals aged 16-80 years
 
2. About to commence treatment with feminising hormone therapy with anti-androgens
 
                                                                                                                                                                                                                      |
| Exclusion Criteria:         | 
 
1. Evidence of androgen deficiency at baseline (T<10nmol/L)
 
2. Any contraindications to spironolactone, cyproterone acetate or E2 therapy
 
                                                                                                                                                                                                        |
| Number of Planned Subjects: | 64                                                                                                                                                                                                                                                                                                                                                                                                             |
| Safety considerations:      | 
Regular monitoring for adverse physiological and psychological effects during routine care of cross-sex hormone therapy, including:
 
 
1. Monitoring of E2 levels
 
2. Monitoring for changes in depression and gender dysphoria
 
                                                                                                                  |

|                      |                                                                                                                                                             |
|----------------------|-------------------------------------------------------------------------------------------------------------------------------------------------------------|
|                      | Ensuring safety when obtaining blood tests.                                                                                                                 |
| Statistical Methods: | Generalised linear mixed model with a restricted maximum likelihood function to determine between group differences in the main outcome measures over time. |
| Subgroups:           | Male-to-female intervention group receiving cyproterone acetate; male-to-female intervention group receiving spironolactone.                                |

## 1. GLOSSARY OF ABBREVIATIONS & TERMS

| Abbreviation | Description (using lay language)                     |
|--------------|------------------------------------------------------|
| CSHT         | Cross-sex hormone therapy                            |
| DXA          | Dual energy X-ray Absorptiometry scan                |
| E2           | Estradiol (the main form of estrogen-female hormone) |
| ECG          | Electrocardiograph                                   |
| GnRH         | Gonadotropin-releasing hormone                       |
| T            | Testosterone (the main male hormone)                 |
| LC-MS        | Liquid Chromatography Mass Spectrometry              |
| PICF         | Participant Information Sheet & Consent Form         |

### 3. INTRODUCTION/BACKGROUND INFORMATION

#### 3.1. LAY SUMMARY

Gender identity is at the core of our sense of self, and considerable scientific evidence supports a biological basis. Gender identity is not chosen, but innate, and differs from biological sex which is determined by sex chromosomes and reproductive organs. Transgender people, whose gender identity is markedly and persistently incongruent with their biological sex, almost always experience gender dysphoria. Characterised by severe distress and discomfort, and the feeling of 'having been born in the wrong body', gender dysphoria compels transgender individuals to seek treatment. For many, aligning their physical characteristics with their gender identity through cross-sex hormones becomes an urgent imperative.

Though international clinical guidelines provide protocols for feminising cross-sex hormone therapy, these recommendations are not evidence-based. Anti-androgen medications (commonly known as testosterone blockers) are commonly used with estrogen as feminising cross-sex hormone therapy in transgender women (males-to-females). The goal of feminising hormone therapy is to increase estrogen, and lower testosterone to achieve hormone levels in the female reference range. Estrogen on its own is usually not effective at completely lowering testosterone levels. As such, anti-androgens are commonly used together with estrogen in order to lower or block testosterone, which in turn aids the development of a feminine body shape, breast development, skin and hair changes. The two most commonly used anti-androgen medications in Australia are cyproterone acetate and spironolactone, however no research exists to show which drug is more effective.

The primary aim of this study is to compare the effectiveness of additional anti-androgen treatment (cyproterone acetate versus spironolactone) to cause breast growth, lower testosterone levels and aid development of feminine body composition changes.

Given a profound lack of research, the need for specific, rigorous research to guide hormonal therapy guidelines for the transgender community is very much needed. The results from the study will inform clinical care and treatment choice for both trans and gender diverse individuals undergoing feminising hormonal treatments as well as their treating clinicians.

#### 3.2. INTRODUCTION

Partly due to increasing societal acceptance, there has been a ten-fold increase in transgender individuals seeking cross-sex hormonal therapy in the last 5 years in Victoria, with an estimated 0.6% - 3% of the population identifying as transgender. (1-3) There is a profound

lack of quality research in optimal cross-sex hormone treatment regimens. Our research seeks to address the medical aspects of gender transition: to improve and optimise evidence-based hormonal treatment guidelines, ensuring suitable standards of care for this marginalised population that experiences significant health inequities, with high prevalence of depression and suicidality, difficulty accessing hormone treatment, and issues with treatment side-effects.

Feminising cross-sex hormone therapy with estradiol (E2), improves psychological functioning in male-to-female transgender individuals (4); however, E2 alone is usually insufficient to lower total testosterone (T) levels. As the large majority of individuals (82% in our cohort, similar to international data) do not undergo genital reassignment surgery to remove the testes (responsible for >95% of T production), anti-androgens (cyproterone acetate or spironolactone) are commonly added to E2, lowering or blocking T to aid development of feminine body composition, facial and body hair and skin.

Preliminary data from our retrospective audit (5) of 540 individuals (n=80 male-to-female on E2 for >6 months) suggest that on univariate and multivariable analyses, the cyproterone acetate group had significantly lower total T levels (overall  $p<0.0002$ ) than the spironolactone group and the E2 alone group. **Ninety per-cent** of the cyproterone acetate group and 40% of the spironolactone group had total T levels < 2 nmol/L. This preliminary study also found that serum urea level was higher (5.2 vs 4.4 mmol/L,  $p=0.035$ ) in the spironolactone group. No differences were observed in total daily oral E2 valerate dose, E2 level achieved, blood pressure, creatinine, or liver function. Supporting our findings, a recently published US retrospective audit of 98 male-to-females found only a quarter of those on spironolactone achieved T in the female reference range (6). Given the limitations of retrospective cross-sectional studies with potential for bias associated with choice of anti-androgen treatment, and the fact that T was measured by immunoassay which lacks precision at low serum T concentrations (as opposed to more sensitive liquid chromatography-tandem mass spectrometry (LC-MS), a prospective randomised double-blind trial to evaluate the optimal anti-androgen agent is warranted.

### 3.3. BACKGROUND INFORMATION

#### ***Goals of feminising cross-sex hormone therapy with E2***

Male-to-female individuals who opt for gender transition are treated with E2, to achieve E2 levels in a female reference range and lower T levels from a male (10–30 nmol/L) to a female range (< 2 nmol/L). Over 3–24 months, individuals develop softening of skin, a decrease in facial and body hair growth, changes in body fat and muscle distribution (such as a lower waist-to-hip ratio and increased total body fat predominantly in a leg and gynoid region), as

well as breast development. (7) E2 negatively feedbacks to suppress gonadotropin-releasing hormone (GnRH), in turn lowering T to a degree, however most individuals will require treatment with an additional anti-androgen drug (cyproterone acetate or spironolactone).

### ***Anti-androgen therapy***

Cyproterone acetate is a steroidal anti-androgen and works in two ways. First, it is a potent peripheral androgen receptor competitive antagonist ( $IC_{50} = 7.1 \text{ nmol/L}$ ) acting at peripheral sites (i.e. skin, hair, body fat, muscle) to decrease the effect of T. Second, it activates the progesterone receptor which, similar to E2 treatment, causes further negative feedback to suppress GnRH and gonadotropins at the hypothalamus/pituitary respectively to lower T production (typically, if added to E2 to  $< 1 \text{ nmol/L}$ ) (8, 9). Notably, although used in Europe for many years, cyproterone acetate is not available in the USA for commercial reasons. This confers a distinctive opportunity to study its effects in Australia.

Spironolactone is a mineralocorticoid receptor antagonist and is anti-androgenic in four ways. First, it is a peripheral androgen receptor partial antagonist ( $IC_{50} = 77 \text{ nmol/L}$ ). The  $IC_{50}$ , which is the concentration of an inhibitor where the binding is reduced by half, is higher than that of cyproterone acetate, reflecting less potency. Second, Spironolactone is a weak inhibitor of  $17\alpha$ -hydroxylase and  $17,20$ -lyase (enzymes in the T biosynthetic pathway) which lowers T to a small degree. Third, it has weak progestogenic activity with a very low half-maximal potency (10); and fourth, it has estrogenic activity expected to suppress GnRH and gonadotropins at the hypothalamus/pituitary (10). However, even at high doses, small pharmacokinetic studies in healthy males show no significant reduction in serum T (despite a transient rise in FSH and LH in the first 2 days of administration) (11, 12). Interestingly, administration of the main metabolite of spironolactone, canrenone, appears to decrease T by 50–60% within hours in healthy men (13) and in conjunction with E2, spironolactone decreases T (14). As spironolactone may potentially cause feminisation by direct antagonism of the androgen receptor without reduction of serum T, it is unclear which anti- androgen is more effective at feminisation, and prospective studies are required. Whilst both anti- androgen agents, cyproterone acetate and spironolactone, have been shown to lower T levels if added to E2 treatment, there have been no head-to-head studies comparing the superiority of one anti-androgen to another (15).

### ***Breast effects of anti-androgen therapy***

Breasts are extremely important for femininity, identity, and self-confidence and an important component of transitioning from male to female. There are no studies comparing cyproterone acetate or spironolactone on breast development. A European observational study demonstrated that only modest increases in breast circumference occur after 1 year of

feminising hormone therapy (16). Noting that relatively low doses of E2 were used (75% below current recommended E2 target range), only 9% developed a bra cup size of A or greater, well below the average female cup size of C. Most breast development occurred in the first 6 months. (16) Although anecdotally, there have been reports that progesterone may enhance breast growth, there are no well-designed studies to assess the effectiveness or refute the lack of effectiveness of progesterone on breast development. (15) As a primary endpoint, we will evaluate the effect of cyproterone acetate, which has progestogenic as well as anti-androgenic activity, on breast size.

### ***Sexual dimorphism and immunity***

Sexual dimorphism in immunity refers to the differences that occur in disease incidence and clinical manifestations between males and females. (17) Indeed, studies have shown that males are more susceptible to bacterial, viral, fungal and parasitic infections as well as malignancy than women. (17) Autoimmune diseases also frequently display significant sexual dimorphism, with conditions such as Graves' disease and rheumatoid arthritis more common in women, and others such as ankylosing spondylitis more common in men. (18) This variation has previously been partly attributed to differences in sex chromosomes, sex hormones (such as testosterone, estradiol and progesterone) and epigenetics. (17, 19) Due to the binary definition of sexual dimorphism, there is little understanding of how transgender individuals receiving hormone therapy fit into the current understanding of sexual dimorphism. In particular, the effects of hormone therapy in transgender individuals on innate immune function, susceptibility to infection, malignancy and autoimmune disease are unclear and warrant further investigation. This will be explored in collaboration with colleagues at the Murdoch Children's Research Institute.

## **4. STUDY OBJECTIVES**

### **4.1. HYPOTHESIS**

In male-to-female individuals commencing estradiol therapy for feminisation, additional cyproterone acetate will be more effective than spironolactone in (a) increasing breast volume and feminine fat distribution (increasing gynoid and leg regional fat), and (b) lowering endogenous testosterone levels,

### **4.2. STUDY AIMS**

1. To compare the effectiveness of cyproterone acetate versus spironolactone as an anti-androgen agent used in cross-sex hormone treatments in male-to-female transgender individuals.

### 4.3. OUTCOME MEASURES

#### 1. Primary Endpoint

- Breast volume

#### 2. Secondary endpoints

- Percentage of individuals who have total T levels < 2 nmol/L (above the female reference range) at 3 and 6 months. ;
- Fat mass including leg and gynoid regional fat;
- Patient Health Questionnaire 9 (PHQ-9) (20)
- Gender dysphoria using the Gender Preoccupation and Stability Questionnaire (GPSQ) (21).

**Covariates:** Age and Body Mass Index (BMI, kg/m^2)

## 5. STUDY DESIGN

### 5.1. STUDY TYPE & DESIGN & SCHEDULE

This is a double-blind, randomised trial in adults aged 16-80 years to compare the anti-androgen effects of 6 months of cyproterone acetate versus spironolactone in 64 male-to-female transgender individuals on E2 therapy. This is a single site study.

#### STUDY VISITS

| Assessment/
Procedure                             | Screening | Visit 1
(0 months) | Visit 2
(1 month) | Visit 3
(2 months) | Visit 4
(3 months) | Visit 5
(6 months) |
|------------------------------------------------------|-----------|-----------------------|----------------------|-----------------------|-----------------------|-----------------------|
| Informed Consent                                     | x         |                       |                      |                       |                       |                       |
| Demographic Information & assessment for eligibility | x         |                       |                      |                       |                       |                       |
| Clinical assessment including chest circumference    |           | x                     |                      |                       | x                     | x                     |
| Depression & gender dysphoria questionnaires         |           | x                     |                      |                       | x                     | x                     |

|                                                  |  |   |   |   |   |   |
|--------------------------------------------------|--|---|---|---|---|---|
| Blood Collection                                 |  | x | x | x | x | x |
| DXA body composition                             |  | x |   |   |   | x |
| Indirect breast anthropometry/ chest photography |  | x |   |   |   | x |
| Blood pressure (safety measure)                  |  | x |   |   | x | x |
| Electrocardiograph (ECG)                         |  | x |   |   |   | x |

## 5.2. STANDARD CARE AND ADDITIONAL TO STANDARD CARE PROCEDURES

| Standard Care Procedures |              |                       | Additional To Standard Care                      |               |               |
|--------------------------|--------------|-----------------------|--------------------------------------------------|---------------|---------------|
| Procedure                | Time(months) | Dosage/Volume         | Procedure                                        | Time (months) | Dosage/Volume |
| Anti-androgen drug       | 0 - 6        | As per standard doses |                                                  |               |               |
|                          |              |                       |                                                  |               |               |
| Blood collection         | 0,1,2,3,6    |                       | DXA                                              | 6             | 0.004 mSv     |
| DXA                      | 0            | 0.004 mSv             | Questionnaires: PHQ-9 & GPSQ                     | 0,3,6         |               |
|                          |              |                       | Indirect breast anthropometry/ chest photography | 0, 6          |               |
|                          |              |                       | ECG                                              | 0, 6          |               |

### 5.3. RANDOMISATION

Participants will be individually randomised by a third party to intervention group 1 (cyproterone acetate 12.5mg daily) or intervention group 2 (spironolactone 100mg daily) in a 1:1 ratio according to a computer generated randomisation procedure, stratified in blocks for baseline age (< 27 and > 27 year-old) and BMI (<24.7 > 24.7 kg/m^2), with cut-offs corresponding to medians found in our previous studies of these individuals. A block size of 2 is chosen, with intervention group allocation randomly permuted and balanced within blocks. Low dose cyproterone 12.5mg has been chosen as this is effective, and reports of meningioma have occurred with higher doses >25mg daily (22). Austin Health Pharmacy Clinical Trials Team will prepare spironolactone 100mg or cyproterone acetate 12.5mg in matching identical capsules. All participants will receive standard care, which will include E2 valerate 4mg daily or equivalent transdermal E2 as an initial dose as per current guidelines (23). A nocte dose will be used so that early morning fasting blood tests will reflect peak serum E2 levels. As per standard clinical care, the E2 valerate dose will be monitored monthly in the first 3 months to ensure serum E2 levels remain in the target range of 250–600 pmol/L (23). The dose will be increased by 2mg each month if levels are below the target range.

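### A fixed block size of 2, written into the protocol of a single-site trial, means that whatever exposes one participant's drug also exposes the block partner's

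*Protocol*

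**What the plan says.** Protocol section 5.3 allocates participants "in a 1:1 ratio according to a computer generated randomisation procedure", "stratified in blocks for baseline age (< 27 and > 27 year-old) and BMI". The BMI bounds read "BMI (<24.7 > 24.7 kg/m 2". Two factors with two levels each give four strata. The block size is fixed and disclosed: "A block size of 2 is chosen, with intervention group allocation randomly permuted and balanced within blocks". No other section varies or conceals it.

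The same section gives the safeguards: "Participants will be individually randomised by a third party", and the pharmacy trials team "will prepare spironolactone 100mg or cyproterone acetate 12.5mg in matching identical capsules". Section 5.1 describes a double-blind trial at one site.

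Three other places matter:

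- Section 9.1 sends sex steroid results to the participant's medical record and study file. It describes no step that withholds testosterone from the people who treat or assess participants.
- Section 8.1 expects testosterone below 2 nmol/L in 48% on spironolactone and 90% on cyproterone. Section 3.2 gives 40% and 90%.
- Section 8.3 adjusts the models for the randomisation strata.

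**The concern.** With 1:1 allocation, a block of 2 can only be AB or BA, so the second allocation follows from the first with certainty. At one site, the people who recruit and follow participants can know the order of enrolment and each person's age and BMI, and so can work out who is paired with whom. The protocol tells them the block size.

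Two things are at stake. If a drug is revealed or guessed before the partner enrols, the partner's allocation is no longer fully concealed. If it is revealed later, the partner's blinding is weakened for the rest of follow-up. Several outcomes could respond to such knowledge: circumference and photographic breast measurements, the satisfaction scale, PHQ-9 and GPSQ.

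A smaller matter is that both stratum definitions use strict inequalities on each side of the cut-off. As written, age 27 and BMI 24.7 belong to no stratum. The cut-offs are medians of earlier cohorts ("with cut-offs corresponding to medians found in our previous studies of these individuals"), so values at or near them are to be expected.

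**Working it through.** **Inputs.** Block size 2, ratio 1:1 and four strata (section 5.3); 64 participants (section 8.1); rates below 2 nmol/L of 48% and 90% (section 8.1), or 40% and 90% (section 3.2). The block size is a design choice, so there is no stated figure for it to reproduce. The enrolment total does reproduce: 25/0.8 = 31.25, rounded up to 32 per group, gives 64.

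**1. Worst case: all earlier allocations known.**

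- Block of 2: the first guess is right with probability 0.5 and the second with probability 1. The average is (0.5 + 1)/2 = 75%, and half of the allocations in complete blocks are forced.
- Block of 4: success by position is 1/2, 2/3, 2/3 and 1. The average is 2.833/4 = 71%. The last position is always forced and the third with probability 1/3, so 1.333/4 = 33% are forced.
- Block of 6: enumeration gives 68% correct and 25% forced.

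With 64 participants spread at random over four equally likely strata (an assumption), on average 2 strata end on an odd number. The expected number of forced allocations is (64 − 2)/2 = 31, with a range of 30 to 32.

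**2. What one testosterone result reveals.** With equal allocation, Bayes' rule gives:

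| Result | Points to | Rates 48% / 90% | Rates 40% / 90% |
|---|---|---|---|
| T ≥ 2 | spironolactone | 0.52/(0.52 + 0.10) = 84% | 0.60/(0.60 + 0.10) = 86% |
| T < 2 | cyproterone | 0.90/(0.90 + 0.48) = 65% | 0.90/(0.90 + 0.40) = 69% |

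**3. What passes to the partner.** Suppose the first member of a block has T ≥ 2, so that P(spironolactone) = 0.839. The probability that the second member is on cyproterone is then:

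- block of 2: 0.839 × 1 + 0.161 × 0 = 84%
- block of 4: 0.839 × 2/3 + 0.161 × 1/3 = 61%
- block of 6: 0.839 × 3/5 + 0.161 × 2/5 = 57%

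**4. What a discordant pair reveals.** If one member of a known pair has T ≥ 2 and the other T < 2, the assignment with spironolactone high and cyproterone low has weight 0.52 × 0.90 = 0.468. The reverse has weight 0.48 × 0.10 = 0.048. Both drugs are then identified with probability 0.468/0.516 = 91%. With the 40% rate it is 0.540/0.580 = 93%.

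**5. A less extreme guess rate.** Guessing a drug from testosterone alone is right (0.90 + 0.52)/2 = 71% of the time. If the partner's drug is predicted only from that, the average over a block of 2 is (0.50 + 0.71)/2 = 60%, against the 75% ceiling.

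Steps 2 to 5 apply the protocol's planning rates to whichever result is seen. The audit behind those rates covered people on estradiol for more than 6 months, so separation at an early visit may be weaker.

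**The case against.** The strongest counter-argument is that the first allocation is normally hidden. A third party randomises, the capsules look the same, and nothing in the protocol shows recruiters an allocation. Section 7.1 also expects hyperkalaemia to be rare with normal renal function and not to affect blinding. This stands, and it is why the 75% and 31 of 64 are ceilings and not forecasts.

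A reader might infer that recruiters could routinely accept or defer the next person knowing the drug. The documents do not support that, mainly because of timing. The first on-treatment blood is at month 1. Section 6.1 reports about 6 new starters a month. If all were eligible and spread evenly over four strata (both assumptions), each stratum would receive 1.5 a month. The chance that the partner enrols before month 1 is then 1 − exp(−1.5) = 78%; at half that rate it is 1 − exp(−0.75) = 53%. If testosterone is first reported at month 3, these become 1 − exp(−4.5) = 99% and 1 − exp(−2.25) = 89%. Most partners would already be randomised. Timing does not protect blinding during follow-up, however: a pair can be exposed at any visit.

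A reader might also infer that a testosterone result reveals the drug. It does not: T < 2 points to cyproterone at only 65%.

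On the strata, a reader might infer that participants at the cut-offs will corrupt the adjusted analysis. That goes too far. With exact decimal age the gap is almost empty, an equals sign may have been lost when the PDF was read, and adjusting for the stratum actually used would be valid under either convention.

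Finally, very small blocks do keep four strata of about 16 closely balanced. That is a genuine benefit, but a small one.

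**Conclusion.** The point holds as a conditional risk. Section 5.3 fixes and discloses a block size under which knowledge of one participant transfers in full to one other. Any unblinding exposes two people instead of one. Testosterone results in the medical record add a softer leak: about 84% for a result of 2 nmol/L or more, transferred undiluted to the partner, against about 61% in a block of 4. These figures rest on the protocol's planning rates and on someone being able to reconstruct the pairs.

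The documents do not show that concealment or blinding has failed, or that half of the allocations are predictable in practice. This should be changed because the change is cheap, but it is not fatal to the trial. The gap at age 27 and BMI 24.7 is in the text as given. It is a minor wording matter whose size depends on how age and BMI are recorded: with age in completed years every 27-year-old is affected, and with decimal age almost nobody is.

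**What to change.** For all allocations not yet made, have the third party generate randomly varying permuted blocks within strata, for example of 4 and 6. Remove the block sizes from the protocol and hold them only in a restricted randomisation document.

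The cost is a new list and a possible imbalance of 2 to 3 participants within a stratum. In the extreme, with all four strata off by 3 in the same direction, the total would be off by 12, giving 38 versus 26. The precision of a simple comparison would then be that of 4 × 38 × 26/64 = 61.75 equally split participants, or 96.5% of 64. The typical loss would be smaller.

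As a minor clarification, define the strata as age < 27 versus ≥ 27 years and BMI < 24.7 versus ≥ 24.7 kg/m², say how age and BMI are recorded for this purpose, and use the same definitions for the strata adjustment in section 8.3. If participants at a cut-off have already been randomised, record which stratum was used for them.
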